### Harms

The intervention in this study is for women to take part in G-ANC. Some of the components of the intervention are focused on nutrition, birth preparedness, breastfeeding, and postpartum care. Some risks, discomforts, and inconveniences may apply and will be minimized as outlined in
Table 3.

**Table 3. T3:** Risks, discomforts, and inconveniences.

Risk/discomfort/inconvenience	Response to Minimize/Mitigate
**Difference in quality of care compared to conventional individual ANC**	Although it is expected that this intervention will improve quality of care, there is a small risk that women in G-ANC could experience lower quality of care compared to conventional ANC with HEWs. This will be mitigated by encouraging all women to return at any other non-group time if they have questions or concerns. On-site mentorship and orientation will be provided by midwives and project staff during G-ANC sessions and any observed gaps in fidelity will be addressed. the mentorship also focused on quality of ANC during G-ANC including the private clinical consultations.
**Discomfort/emotional distress from discussing sensitive or difficult topics**	Potential topics of discussion during group time include experience with poor maternal or neonatal outcomes, gender-based violence, prevention/treatment of HIV, and family planning. Women will never be directly asked of their own status or personal experience. These topics will be discussed in terms of what participants have seen or heard so that discussion can occur in the abstract and need not directly reflect the women present. In addition, women will be encouraged to share only what they are comfortable sharing, and facilitators will be trained to respond to difficult emotional situations. Women will be counseled on the importance of confidentiality and privacy during the first G-ANC meeting.
**Time spent at the HP**	It is possible that women who attend G-ANC may be inconvenienced due to the longer time spent at the HP to participate in the meetings. As a mitigation strategy, women will be told the next meeting place and time, connected to peers to encourage each other to arrive on time, and encouraged to start routine G-ANC activities, e.g., “sister up” and peer-to-peer self-assessments as soon as they arrive.
**Breach of confidentiality by other members of group**	If women do opt to share personal information it is possible that that information will be shared by other group members. To mitigate this, group norms will be discussed at every meeting to reinforce that the group meetings are confidential, and information about other women should not be shared outside the group without the woman’s explicit consent. Individual test results will never be shared in the group setting, but rather during the brief private assessment done during each meeting. This is also a time where women can discuss any issues they would like to remain confidential between themselves and the provider. However, confidentiality breaches have not been identified as a significant concern with G-ANC in the literature.
**Breach of confidentiality by study staff**	We will conduct comprehensive training in confidentiality and appropriate research/clinical standards for study staff before the study begins and reinforce this training throughout the study. We do not anticipate any breach of confidentiality on the part of the study staff. Any breach of confidentiality will be met with counseling and support provided by the study and clinical staff. In addition, any study staff responsible for a breach of confidentiality will be disciplined appropriately, up to and including termination of employment.
**Referral**	If a participant needs clinical referral as part of her care, this will be provided to both the control and intervention arms according to standard site protocols and will not be affected by the study.

### Sample size

We used the existing data from Amhara region for two primary study outcomes (i.e., four or more ANC contacts [31.5%] and facility-based delivery [27.1%]) to calculate the number of clusters (i.e., HCs) to be randomized to be able to detect an odds ratio of 2 comparing post-intervention to pre-intervention proportion with 80% statistical power using stepped-wedge design with three time periods and two steps for switching from standard care to intervention (
Figure 1). For the complete stepped-wedge design, the calculations indicate that a sample of 12 HCs with three time periods/two steps, six HCs switching from control to treatment at each step, and with an average of 30 women per cluster (i.e., three HPs with 10 women in each) per time period achieves 84% power to detect an odds ratio of 2 at 0.05 level of statistical significance. The underlying pre-intervention proportions and the post-intervention proportions associated with odds ratio of 2 are shown in
Table 4.

**Table 4. T4:** Pre-intervention and post-intervention proportions with associated odds ratio.

Study Outcome	Pre-Intervention Proportion, P2 ( Table 1)	Odds Ratio to be Detected	Post-Intervention Proportion, P1
Four or more ANC contacts	0.315 (Amhara)	2	0.48
Facility-based delivery	0.271 (Amhara)	2	0.43

The within-HC correlation (intraclass correlation coefficient [ICC]) is assumed to be 0.100. This level of correlation is consistent with the one reported by Ousman
*et al.*, where clustering was done at enumeration-area level with an ICC of 0.11 for ANC visits (
Ousman *et al.*, 2019). The total sample size for ANC clients is then 12 HCs x 3 HPs x 10 women/HP x two time periods = 720 women. An odds ratio of 2.0 translates to 50%–60% improvement in completion of four or more ANC contacts and 60%–70% improvement in facility-based delivery in the G-ANC arm compared to pre-intervention.

The study will be conducted in 12 HCs. The overall sample size is a total of 770 women. The pilot will enroll 50 women (i.e., 10 women per HP, five HPs), and the randomized control trials will include a maximum of 720 women (
Table 5). Sample size for the qualitative data collection is indicated in
Table 6.

**Table 5. T5:** Number of HCs, HPs, and women included in the G-ANC study.

	Pilot	Time parried 1 Control	Time Period 2 (control + intervention)	Time Period 3 (intervention)	Total
HC	2	6	12	6	**14**
HP	5	18	36	18	**41**
Women	50	180	360	180	**770**

**Table 6. T6:** Summary of sample size for qualitative data collection.

Study population	Estimated number of IDIs per round of data collection (after pilot, after T2 and after T3)	Total
Women who completed most G-ANC meetings	Up to 9, in 3 rounds	27
Women who dropped out of G-ANC after 1–2 meetings	Up to 9, in 3 rounds	27
Women who completed most G-ANC meetings, but did not give birth in a health facility	Up to 9, in 3 rounds	27
Women who completed most G-ANC meetings and gave birth in a health facility	Up to 9, in 3 rounds	27
HEWs	Up to 5, in 3 rounds	15
Health facility managers	Up to 1 per facility, 18 HPs T2 and 18 HPs T3	36
District/Regional managers	Up to 1 per woreda manager Up to 1 per regional manager	15 3

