### Study implementation

Group ANC at the HP level is a new intervention, therefore the study will be rolled out using a phased approach.

**
*Pilot phase*:** Prior to study activation, we will pilot G-ANC in up to five purposively selected HPs in Amhara region that will not be included in the study. This pilot phase will allow us to adapt G-ANC materials to adjust for the literacy levels of the HEW and conditions at the HP. After the materials have been adapted, up to two HEWs per HP (total 10 HEWs) will be trained to facilitate G-ANC. In the pilot phase, we will enroll a maximum of 50 women (up to 10 per HP x up to 5 HPs). The pilot phase will determine feasibility, i.e., whether HEWs are able to facilitate the G-ANC meetings, there are enough eligible ANC clients at the HP level, we are able to enroll enough women at the HP who are of a similar gestational age, and women come back to the HP for the G-ANC meetings. After completing at least two G-ANC meetings in the pilot, we will determine the feasibility of moving to Phase 2 of the study. Training modules, data collection tools, and intervention delivery models will be refined, with the added engagement of midwives and health staff, based on pilot study feedback.

**
*Trial phase*:** Phase 2 includes T1, T2, and T3. During T1, pre-intervention data will be collected from the first set of 18 HPs by interviewing pregnant women during their pregnancy and again postpartum. The women in T1 will not receive the intervention. During T2, the G-ANC intervention will be implemented in the first set of 18 HPs (first six clusters), and pre-intervention data collection will be conducted in the second set of 18 HPs (i.e., second six clusters). During T3, the G-ANC intervention will be implemented in the second set of 18 HPs. If the first set of 18 HPs chooses to continue the G-ANC intervention with a second cohort, an additional six months of data collection will occur during T3. Participant timeline is depicted in
Figure 2.

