### Data collection

Both quantitative and qualitative data collection approaches will be used in this study. Data will be collected in the pilot phase and then during study implementation (Phase 2).

Once enrollment begins, all new ANC attendees in the selected HPs will be screened for eligibility during the first ANC contact with a health care provider. The screening and enrollment questionnaire will be completed. Basic demographic data will be collected from all eligible consented women (all who meet the inclusion criteria). All data will be de-identified for those who decline study participation. Baseline and endline data will be collected from all eligible and voluntary women participating in all study time periods. During the first period, data will be collected from 18 control HPs. In the second period (T2), data will be collected from 18 intervention and 18 control HPs. In the third period, (T3) data will be collected from 18 intervention HPs.

Data quality will be monitored through the use of trained research assistants and supervisors, data quality supervision, and use of an electronic data collection program to minimize data entry errors.

The study team will select respondents for the IDIs at the end of the study based on preliminary findings from the quantitative survey. IDIs with women will be conducted at the end of T2 and T3, after completion of all G-ANC meetings (
Table 7). Specific topics/domains to explore with G-ANC participants include satisfaction with care, any perceived changes in self-efficacy or empowerment, health literacy, improved communication and/or trust with providers and the health system as a whole, factors in uptake/non-uptake of postpartum family planning, and the overall impression of the G-ANC model. In this study, we will use standardized pretested tools to assess the levels of empowerment, self-efficacy, and satisfaction. For empowerment and self-efficacy, we will use eight questions related to their current pregnancy and calculate a composite score to understand the woman's level of empowerment. We will ask 11 questions about their satisfaction with the ANC received during their last pregnancy and with the G-ANC for their current pregnancy.

**Table 7. T7:** Data collection timing, per tool.

Data collection tool	Study participant	Timing of data collection		
		T1	T2	T3*
Cluster level information	HP level information	18 HPs	36 HPs	18 HPs

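### The stated 84% power belongs to a complete 1,080-woman stepped wedge; the planned 720-woman incomplete design has about 35–40% power for an odds ratio of 2 at the protocol's own ICC

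*Protocol article*

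**What the plan says.** The Sample size section aims for 80% power to detect an odds ratio of 2 and describes the design behind its result in these words: "For the complete stepped-wedge design, the calculations indicate that a sample of 12 HCs with three time periods/two steps". It takes half of the HCs to start G-ANC at each step, and every HC to supply about 30 women, ten from each of its three health posts, in every period. On that basis the design is said to reach its power: it "achieves 84% power to detect an odds ratio of 2 at 0.05 level of statistical significance". The ICC within HC is assumed to be 0.100. Table 4 gives 0.315 rising to 0.48 for four or more antenatal care (ANC) contacts, and 0.271 rising to 0.43 for facility-based delivery.

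After the ICC is stated, the total is given as "12 HCs x 3 HPs x 10 women/HP x two time periods = 720 women". The section later calls 720 a maximum, and Table 5 splits it as 180, 360 and 180 women in T1, T2 and T3.

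The other sections agree with Table 5. Study implementation says "During T1, pre-intervention data will be collected from the first set of 18 HPs", and the second set is first observed at T2. Data collection says "In the third period, (T3) data will be collected from 18 intervention HPs". Study design and Study implementation let the first-set sites choose to run a second G-ANC cohort in T3, with data collected if they do. The Data analysis section specifies a logit mixed model with intervention, period and their interaction as predictors and a random intercept for HC.

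**The concern.** The power figure and the sample size sit close together and read as one calculation, but they describe two designs. The power uses six cells (two sequences by three periods). The plan fixes four of them, so one third of the data behind the 84% is not planned.

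The loss is much more than a third of the information. In a stepped wedge adjusted for period, the effect is identified by comparing clusters under different conditions in the same period, and by changes within clusters measured against clusters observed in the same periods. Here T1 is observed in one sequence only and T3 in the other only, so neither has a comparator.

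At stake is how both primary outcomes are interpreted. The results are meant to inform whether G-ANC at health posts becomes policy, and a non-significant result looks quite different against 84% power than against less than half of that.

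**Working it through.** **Inputs (Sample size section).** Six HCs per sequence; m = 30 women per HC-period; ICC ρ = 0.10; control proportions p0 = 0.315 and 0.271; odds ratio 2; alpha 0.05, taken as two-sided because the text does not say. The exact proportions at odds ratio 2 are p1 = 2p0/(1 + p0) = 0.4791 and 0.4264, so the differences are d = 0.1641 and 0.1554.

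**Method.** Hussey–Hughes generalised least squares on the proportion scale, with fixed period effects and an HC random intercept. Total variance is σ² = p0(1 − p0), of which ρσ² is between HCs. Power = Φ(d/SE − 1.96).

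**Step 1: reproduce the stated figure.** Complete design, with sequences control–G-ANC–G-ANC and control–control–G-ANC, 1,080 women:
- Four or more ANC contacts: SE 0.0556, z = 2.95, power 83.9%.
- Facility-based delivery: SE 0.0532, z = 2.92, power 83.1%.

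With Table 4's rounded proportions the results are 84.3% and 84.8%. The stated 84% is therefore reproduced for the complete design. Variance at the average of p0 and p1 gives 79.9% and 77.7%.

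**Step 2: the planned four cells.** Set 1 is control at T1 and G-ANC at T2; set 2 is control at T2 and G-ANC at T3. The mean of the six HCs seen at T1 is absorbed by the T1 period effect, and likewise at T3. The weights per HC on the treatment effect are 0 at T1, +1/6 for set 1 at T2, −1/6 for set 2 at T2, and 0 at T3. The estimate is thus a parallel comparison at T2, 180 versus 180 women, and its variance has a closed form:

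SE² = 2σ²[1 + (m − 1)ρ]/180, with design effect 1 + 29 × 0.1 = 3.9.

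- Four or more ANC contacts: σ² = 0.315 × 0.685 = 0.2158; SE = √(2 × 0.2158 × 3.9/180) = 0.0967; z = 0.1641/0.0967 = 1.70; power 39.6%.
- Facility-based delivery: σ² = 0.271 × 0.729 = 0.1976; SE = 0.0925; z = 0.1554/0.0925 = 1.68; power 39.0%.

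Variance at the average proportion gives 36% and 35%. A t reference on 10 degrees of freedom (12 HCs) gives about 29–34% over both variance conventions. A linear time term in place of categorical periods gives the same power as the T2 comparison.

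**Step 3: sensitivity to the ICC.** Four cells, normal reference, range over both outcomes and both variance conventions:

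| ICC | Power for odds ratio 2 |
|---|---|
| 0.10 | about 35–40% |
| 0.05 | about 51–57% |
| 0.02 | about 69–76% |
| 0.01 | about 78–84% |

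**Step 4: the optional T3 cohort.** If all six first-set HCs continue (five cells, 720 + 180 = 900 women), T3 contains both sequences and earlier periods regain weight. Power at ICC 0.10 is 75.7% and 74.8%, or 71% and 69% with average-proportion variance.

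**Step 5: detectable effect.** With four cells and ICC 0.10, 80% power needs an odds ratio of about 3.0–3.4 (normal reference) or 3.4–3.9 (t on 10 degrees of freedom), depending on outcome and variance convention.

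**The case against.** The strongest reply is that the design is not closed at four cells. First-set sites may run a second cohort in T3, and at the article's status date T3 had not begun, so its final extent cannot be known from the document. With full uptake, power is about twice the four-cell figure and close to the target. This stands as a reason to report that scenario and not to call 35–40% the power of the trial without qualification. It does not rescue the 84%: the cohort depends on the sites' choice, lies outside the stated maximum of 720 and the 18 health posts counted for T3, and even with full uptake stays below 80%.

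Second, the four-cell result depends heavily on the ICC, and the source cited for 0.10 measured clustering in enumeration areas, not HC catchments. This also stands, and calls for a range. But 0.10 is the protocol's own value, and power nears 80% only at an ICC of about 0.01.

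Third, before-and-after information within HCs might seem to help. It would do so only if period effects were dropped, and the planned model includes them. The planned intervention-by-period interaction makes matters no better, since only T2 holds both conditions.

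Two stronger readings are tempting. A reader might infer that the 84% was miscalculated; it was not, and the text labels it as the complete design's. A reader might also infer that the investigators will treat a null result as proof of no effect; no section says so.

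**Conclusion.** The point holds. The 84% is right for the design it names and does not apply to the one planned. At ICC 0.10 with period in the model, the 720-woman design has about 35–40% power for an odds ratio of 2 on each primary outcome (29–34% with the t reference). Under those assumptions, a true doubling of the odds would be missed about six times in ten.

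The conclusion assumes a two-sided 0.05 test, 30 women per HC-period, equal cluster sizes and no loss to follow-up. The size of the shortfall depends on the ICC and on uptake of the optional T3 cohort. Because the stated power of both primary outcomes is affected, the statement must be corrected.

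**What to change.** In the Sample size section, replace the 84% sentence with the power of the design as planned, for example: with first-set HCs observed in T1 and T2, second-set HCs in T2 and T3 (720 women), period effects in the model and ICC 0.10, power for an odds ratio of 2 is about 35–40% for each primary outcome, or 29–34% with a t reference on 10 degrees of freedom. Then:

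- Add the ICC range from the table in the working.
- Give the power if all first-set HCs take up the T3 cohort (900 women, about 69–76% at ICC 0.10), and say that this cohort is optional and outside the 720.
- If a detectable effect is quoted, name the reference distribution and variance convention beside it.
- State that, at this power, a non-significant result is not evidence of no effect.

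The 84% may be kept only if it is marked as the figure for a complete design that the trial does not plan to run. The cost is rewording and a less favourable stated figure; enrolment does not change.

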**Figure 2. f2:**
[figure not shown]
G-ANC study timeline with pilot and trial phases.

Once study participants are enrolled, the participant timeline is about 8.5 months: enrollment with a baseline questionnaire, follow-up for about six months during ANC, and endline survey up to six weeks post-delivery. Participants in the qualitative research will have a single contact for the IDIs.

The overall duration of the entire study is 25.5 months. The implementation process will be documented in these sites, with some corrective measures expected to be taken after each block, depending on implementation process documentation, findings from pause and reflect sessions, and qualitative study findings before commencing the next block. A transition plan will also be developed by Jhpiego to hand over implementation to the government.

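### The stated 84% power assumes full cohorts and complete follow-up: 30 women per health center per period is both the power input and the enrolment ceiling, with nothing allowed for loss before the postpartum endline

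*Protocol article*

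**What the plan says.** The Sample size section of the protocol article sets out to detect an odds ratio of 2 "with 80% statistical power using stepped-wedge design with three time periods and two steps". It reports the result as follows: "For the complete stepped-wedge design, the calculations indicate that a sample of 12 HCs with three time periods/two steps", six HCs switching at each step, "with an average of 30 women per cluster (i.e., three HPs with 10 women in each) per time period achieves 84% power". The intraclass correlation is taken as 0.100 and the significance level as 0.05.

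The same section then gives the trial size as 12 HCs × 3 health posts × 10 women × 2 periods = 720, and adds that "the randomized control trials will include a maximum of 720 women". Table 5 divides these into 180 women in T1 (6 HCs), 360 in T2 (12 HCs) and 180 in T3 (6 HCs).

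The Study design and Intervention sections describe group cohorts of eight to 10 women per health post. Two more may join by the second meeting. The Study implementation section puts each woman's participation at about 8.5 months: enrolment with a baseline questionnaire, "follow-up for about six months during ANC, and endline survey up to six weeks post-delivery". The Data analysis section mentions multiple imputation for missing covariates.

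**The concern.** A power calculation runs on women who have an outcome. Here its input of 30 per HC-period is carried unchanged into the enrolment count, and that count is described as a maximum. Pregnancy loss, moving away, withdrawal or a missed endline can only lower the average analysed below 30, and so can cohorts of eight or nine. The stated calculation has no factor for either.

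What is at stake is a planning figure that readers will use to judge a null or imprecise result. The margin between the reported 84% and the 80% target is four points, so it matters how much shortfall that margin can bear.

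**Working it through.** **Inputs (Sample size section and Tables 4 and 5).** Control proportions p0 = 0.315 (four or more visits) and 0.271 (facility delivery). Odds ratio 2 gives p1 = 2p0/(1 + p0) = 0.4791 and 0.4264; Table 4 rounds these to 0.48 and 0.43. ICC 0.10, 12 HCs, three periods, six HCs switching per step, 30 women per HC-period. The 0.05 level is taken as two-sided, because sidedness is not stated.

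**Step 1: enrolment ceiling against power input.** Table 5 has 6 + 12 + 6 = 24 HC-periods, and 720/24 = 30. The ceiling on the average equals the power input.

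**Step 2: reproduce the 84%.** The method is Hussey–Hughes, with free period effects, a random HC intercept and the total variance set at the control rate:

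- total variance = p0(1 − p0)
- between-HC variance τ² = 0.10 × total variance
- variance of an HC-period mean around its HC, s = 0.90 × total variance / m
- for the complete design with these sequences, Var(effect) = s(s + 3τ²) / [3(s + 2τ²)]
- power = Φ(|p1 − p0| / SE − 1.96)

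For four or more visits at m = 30, total variance = 0.315 × 0.685 = 0.2158, τ² = 0.02158 and s = 0.00647. Then Var = 0.00647 × 0.07121 / (3 × 0.04963) = 0.00309, SE = 0.0556, z = 0.1641/0.0556 = 2.95 and power = 83.9%. The stated figure is reproduced. Other variance conventions give 70–81% at m = 30; they do not reproduce 84% and are not used here.

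**Step 3: lower the number analysed.** The article gives no loss rate, so 27 and 24 are assumed values. They correspond to 10% and 20% loss, or to an average of nine or eight women per health post.

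| Outcome (p1 used) | m = 30 | m = 27 | m = 24 | m giving 80% | Shortfall from 30 |
|---|---|---|---|---|---|
| 4+ visits (0.4791) | 83.9% | 80.1% | 75.5% | 26.96 | 10.1% |
| 4+ visits (0.48) | 84.3% | 80.5% | 76.0% | 26.65 | 11.2% |
| Facility delivery (0.4264) | 83.1% | 79.3% | 74.7% | 27.53 | 8.2% |
| Facility delivery (0.43) | 84.8% | 81.0% | 76.5% | 26.25 | 12.5% |

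**Step 4: the same method on the planned cells.** A complete design with these inputs would need 12 × 3 × 30 = 1,080 women. The 720 in Table 5 observe the first six HCs in T1 and T2 only, and the second six in T2 and T3 only. With free period effects, T1 and T3 are each seen in one sequence alone and cannot separate period from intervention. What remains is the T2 comparison of six HCs with six, so Var(effect) = (s + τ²)/3. For four or more visits at m = 30 this is (0.00647 + 0.02158)/3 = 0.00935, SE = 0.0967, z = 1.70 and power = 39.6%.

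| Outcome (p1 used) | m = 30 | m = 27 | m = 24 |
|---|---|---|---|
| 4+ visits (0.4791) | 39.6% | 38.8% | 37.8% |
| 4+ visits (0.48) | 40.0% | 39.2% | 38.2% |
| Facility delivery (0.4264) | 39.0% | 38.2% | 37.2% |
| Facility delivery (0.43) | 40.5% | 39.6% | 38.6% |

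Here τ² is more than three times s, so losing women within HCs changes little; a 20% shortfall costs about two points.

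**The case against.** A reader might infer that the 84% cannot be met on the plan's own calculation. The article does not support that. No loss rate is given, the arithmetic is sound at 30 women, and with full cohorts and negligible loss the figure is reached. The design target is 80%, and the margin above it absorbs roughly 8–12%. With Table 4's rounded proportions, a 10% loss still leaves 80.5% and 81.0%.

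A second argument is that an attrition allowance is the sort of detail an article leaves to the full protocol. That would hold if the section were silent on how 720 was reached. It is not: it prints the whole product and a maximum, and the product equals the power input exactly. The point concerns what is stated.

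Third, the plan does act on retention. Eligibility requires locator information and planned residence for at least 10 months, long absences are excluded, and missed meetings are tracked. These measures make loss smaller but not zero. The two late joiners can raise a single cohort above 10, but the maximum of 720 still holds the trial average at 30. The optional second T3 cohort is not counted in Table 5 or in the 720.

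The objection on materiality largely stands. For the cells that Table 5 plans, attrition costs about two points, and the missing cells account for most of the gap from 84%.

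**Conclusion.** The concern holds in limited form. The 84% is conditional on 30 women with an outcome in every HC-period, and that number is also the ceiling on the average enrolled and the top of the stated cohort range. In the complete-design calculation, power falls from 83–85% at 30 women to 79–81% at 27 and 75–77% at 24, and the 80% target is lost once the combined shortfall passes roughly 8–12%. It would be wrong to say that the figure is unattainable or that 80% is certainly lost.

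Attrition is the smaller of the two reasons the 84% is overstated for this trial. On the planned cells the same method gives about 39–40% at 30 women and 37–39% at 24.

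These results assume a two-sided test, variance at the control rate, free period effects, one ICC within and between periods, and the same shortfall in every HC-period. The eight-to-10 range is stated for group cohorts, so under-filling might affect intervention cells more than control cells. The Table 5 layout is taken without the optional second T3 cohort.

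**What to change.** In the Sample size section, call 720 the number enrolled. Restate power at the expected number of women with an endline outcome per HC-period. Either show 24, 27 and 30 with the loss rates marked as assumptions, or use the endline completion seen in T1 and T2, which the Study status section says have been surveyed.

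Compute the restated figure for the cells actually collected, with each HC in two of three periods. Lowering 30 to 24–27 within the complete-design calculation alone would print about 75–81%, still for a design that is not being run. Name the variance convention and the sidedness so that the number can be checked.

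The cost is one recalculation and a much less favourable stated figure, mostly because of the design rather than the losses. No extra enrolment and no change to procedures are required. With T1 and T2 already surveyed, the restatement mainly serves honest reporting and interpretation of precision.
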